### Anticipated results

We anticipate that the circadian rhythm could predict the change of neurocognitive functioning among BD patients. More evidence of circadian rhythm importance for BD could be provided if the assumption holds.

## Discussion

The importance of circadian rhythm in BD has always been emphasized as BD is somehow rhythmic by itself in clinical oscillations among depressive, hypomanic/manic, and intermittent episodes [62]. The large genome-wide association study (GWAS) has found significant changes in gene expression around circadian rhythm pathways in BD population [63]. We hypothesized that disrupted circadian rhythm also plays a role in neurocognitive functioning impairment in BD. Currently, limited evidence could be cited to support such an opinion. Mice deficient in Vipr2, which participate in internal rhythm synchronization, exhibit cognitive deficits resembling schizophrenia [64,65]. Circadian clock-deficient cryptochrome knockout mice present with cognitive dysfunction and elevated anxiety [66]. Poor sleep quality is found related to poorer neuropsychological functioning in bipolar I disorder [67]. With RDoC highlighting circadian rhythm and cognitive evaluation in arousal/modulatory system and cognitive system separately, we can’t help speculating the role of circadian rhythm in neurocognitive impairment of BD, where we seek to better understand the correlation of circadian rhythm and neurocognitive functioning [11].

Still, we have not seen any study investigating the long-term neurocognitive predictability by circadian rhythm in BD patients. Thus, we designed such a study protocol where we included subjective rhythm questionnaires and objective actigraph data to represent the circadian rhythm. We plan to test our hypothesis from both cross-sectional and prospective perspectives. Specifically, to detect if the disrupted circadian rhythm is cross-sectionally correlated with worse neurocognitive functioning, if the subjectively measured circadian rhythm is comparable to objectively measured circadian rhythm, and if the circadian rhythm is predictive of long-term neurocognitive functioning changes.

This study is novel and intriguing due to the following advantages. Firstly, It is the first study protocol to establish the correlation between daily and seasonal circadian rhythms and neurocognitive functioning among BD patients. Secondly, it uses reliable yet less utilized techniques for evaluation accuracies, such as actigraph and CANTAB tests, with a combination of commonly recognized questionnaires for rhythm and mood evaluations. Thirdly, it is a prospective study lasting 12 months that fits in RDoC matrix, which could efficiently fill in the gap of long-term actigraph and cognitive functioning studies. Our study bears the potential to provide stronger evidence than a cross-sectional design and could enlighten similar designs guided by RDoC recommendations [8].

Our study also has some limitations. Initially, we do not explore the melatonin and cortisol levels fluctuations, which is the strongest indication of circadian rhythm [68]. Since we are not able to provide a laboratory condition for such repetitive samples, we are afraid that outpatients could not complete such a complicated measurement outside the hospital. Also, we did not use a sleep diary out of consideration that BD patients lack motivation with no economic compensation. Fortunately, there are some evidences supporting the comparability of cortisol and melatonin tests and sleep diary by actigraph data [69].

Secondly, this study is not a randomized controlled study, and a lot of facts might add bias to this study. This is a single-center study, and most patients will be recruited from our Bipolar Disorder Specialist Clinic, which is less presentative of real-world situations and might decrease the diversity of treatment procedures and medications. Moreover, to strengthen the validity and reliability of data, we minimized the amount of self-rating questionnaires, thus impeding more involvement of useful questionnaires such as the Athens Insomnia Scale, Biological Rhythms Interview of Assessment in Neuropsychiatry, 32-item Hypomania Checklist, Patient Health Questionnaire-9 and General Anxiety Disorder-7 [60,70–73]. Nevertheless, we argue that this is only an exploratory study. More strict study conditions could be set and adapted based on this small-sample study results.

Finally, there is little information for predicting our results due to lack of enough relevant studies. Therefore, the statistical methods might differ from our original design and should be adapted with our ultimate results.

In summary, this is a 12-month longitudinal cohort study protocol. We aimed to find evidence for circadian rhythm influence on neurocognitive functioning on BD patients. We hypothesize that circadian rhythm could predict the change of neurocognitive functioning. Our findings may provide additional information for BD pathophysiology, treatment targets and prediction. Larger and more homogeneous sample with more integrate design could be considered in future study.

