#### Circadian rhythm assessment

The circadian rhythm variable consists of two components: subjective questionnaires and objective behavioral data. The questionnaires used include the Morningness Eveningness Questionnaire (MEQ), the Pittsburgh Sleep Quality Index (PSQI), and the Seasonal Pattern Assessment Questionnaire (SPAQ). The MEQ is a 19-item self-rating scale used to evaluate chronotype, with scores indicating evening, intermediate, or morning types [35]. The PSQI is an 18-item self-rating scale that assesses sleep quality and disturbances, and a validated Chinese version will be used [36,37]. The SPAQ is a widely used questionnaire for evaluating seasonal effects on mood and behavior. It includes a general seasonality score (GSS) that can be used to screen for seasonal affective disorder (SAD) [38,39]. Except for the SPAQ, all the aforementioned scales and questionnaires have already been validated or translated into Chinese versions.

On the day of evaluation, participants will be asked to wear a wrist-worn actigraph device (wGT3X-BT, v1.9.2, ActiGraph LLC) for 14 consecutive days and nights. The actigraph’s flashing light will be disabled throughout the monitoring period. The device will continuously record physical activity, sleep/wake information and sedentary time using a sampling frequency of 100 Hz. Participants will be instructed to continuously wear the actigraph except during activities such as showering, swimming, or any activity that would consistently expose the device to water for more than 30 min. Data retrieval and analyses will be performed using the ActiLife software program (version 6.13.4) with 60-second epochs [40]. The collected raw data will be stored and analyzed using publicly available algorithms. Non-wear time will be defined as 60 consecutive minutes of zeros with a 2-minute spike tolerance based on the default Wear Time Validation algorithm provided by Actilife 6.13.4. Any non-wearing epochs will be excluded from the analysis without any data imputation [41,42]. For a day to be deemed valid, it must have a minimum of 20 h of wearing time [42]. A participant will be considered valid if they have a minimum of 7 valid days, including at least 5 weekdays and 2 weekend days [35].

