### Sample size calculation

The sample size for this study was determined based on the primary hypothesis. To calculate the sample size, a review of relevant literature was conducted, and the PASS.15 computer software was used. Due to limited available reports, data from a previous study that evaluated changes in SWM between errors after 1 month of olanzapine treatment in 15 unipolar/bipolar depressive patients was used. In that study, the between errors at baseline and 1-month olanzapine treatment were 34 ± 24 and 21 ± 21, respectively (Mean ± Standard Deviation) [59].

With an assumed power of 0.80 and an alpha level of 0.05, it was determined that a cohort size of 41 at follow-up would achieve 80% power to detect a difference of −13 between the null hypothesis (both baseline and 12-month follow-up means of SWM errors are 34) and the alternative hypothesis (mean of 12-month follow-up is 21). The estimated standard deviations were 21 and 21 at baseline and 12-month follow-up, respectively, using a two-sample *t*-test [54]. Considering a potential dropout rate of 50% and the decision not to replace dropout participants, a total of 81 patients at baseline were deemed necessary. Finally, given the large number of outpatient receptions, we plan to recruit 100 participants.

Therefore, the study aimed to recruit a sample size of 100 patients at baseline to account for potential dropouts and achieve the desired statistical power.

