### Statistical analysis

SPSS (version 26) will be used for the analysis of this study. Histograms will be used to determine the normality or approximate normality of the data. This will be achieved by combining them with the Shapiro-Wilk test [60]. Descriptive analyses will be performed to examine participant and disease characteristics, as well as data from clinical, circadian rhythm, and neurocognitive functioning assessments. Missing value analyses will be conducted with multiple imputation or expectation maximization methods to handle any missing data.

Spearman correlations will be employed to compare subjective and objectively assessed circadian rhythm patterns. Subjective assessments include MEQ, SPAQ, and PSQI results, while objective assessments will primarily rely on behavioral data.

Longitudinal analyses will involve calculating changes in SAS, SDS, HAMD, HAMA, and YMRS scores, and correlating these difference scores (baseline minus 6-month follow-up, baseline minus 12-month follow-up) with circadian rhythm parameters for each participant using Spearman correlation. Mixed regression models will be used to determine if changes in circadian rhythm significantly predict changes in neurocognitive functioning from baseline to 6-month follow-up and 12-month follow-up [61]. Stepwise adjustment of covariates will be employed to construct several regression models to explore the robustness of the relationship between circadian rhythm and neurocognitive functioning. Adjustments will be made for other factors that may influence these associations, such as disease duration, age, gender, current medication use, education level, and severity of emotional symptoms.

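### The protocol lets the statistical methods follow the results while the circadian exposure is left unranked, so a significant finding could not support the single hypothesis at a known error rate

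*Protocol article*

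**What the plan says.** At the end of the limitations in the Discussion, the protocol article gives scarce prior evidence as its reason and then states that "the statistical methods might differ from our original design and should be adapted with our ultimate results".

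The exposure is broad. Under Circadian rhythm assessment, "The circadian rhythm variable consists of two components: subjective questionnaires and objective behavioral data". That section goes on to name three questionnaires, four actigraphy sleep parameters, three non-parametric rhythm parameters and two activity-time measures. None is called primary.

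Under Statistical analysis, mixed regression models test whether circadian changes significantly predict cognitive changes from baseline to 6 and to 12 months. Neither follow-up is named as the main one. Then: "Stepwise adjustment of covariates will be employed to construct several regression models to explore the robustness of the relationship".

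Some things are fixed. The Neurocognitive assessment section names one primary outcome, a cognitive composite. The Sample size calculation says: "The sample size for this study was determined based on the primary hypothesis", and sets its error rates in these words: "With an assumed power of 0.80 and an alpha level of 0.05". The Discussion, however, describes the study as merely exploratory.

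**The concern.** A p-value has its nominal meaning only if the test would have been the same whatever the data showed. The Discussion sentence removes that condition. It does not limit adaptation to checks of distributional assumptions, to decisions made before outcomes are examined, or to documented amendments; it ties the choice of method to the results. This is a stated rule and not a detail left for another document: a separate analysis plan could fix every choice, and this sentence would still permit departure from it.

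The room for choice is wide. The hypothesis is a single statement about circadian rhythm, but a dozen measures could stand for it. Even the form of the exposure is unsettled: the objective in the Introduction has circadian rhythm predicting cognitive change, while the analysis section uses changes in circadian rhythm.

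At stake is the study's only hypothesis. A reader who meets one significant association in the final report, alongside a primary hypothesis and an alpha of 0.05, would take it as a 5% test. The plan as written does not make it one.

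**Working it through.** **1. The plan's own alpha.** The 0.05 appears only in the sample size section. Its inputs are the difference ("to detect a difference of −13 between the null hypothesis") and the spread ("The estimated standard deviations were 21 and 21 at baseline and 12-month follow-up, respectively"). Sidedness is not stated; a two-sided test reproduces the figure:

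n = 2 × (1.960 + 0.842)² × 21² / 13² = 2 × 7.849 × 441 / 169 = 40.96, so 41, as stated. With 50% dropout, 41 / 0.5 = 82, against the stated 81, a difference of one patient.

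The figure reproduces, but it concerns spatial working memory errors at baseline against 12 months. It contains no circadian term, so this alpha does not govern any test of an exposure.

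**2. Count of measures** (Circadian rhythm assessment).
- Questionnaires: MEQ, PSQI, SPAQ = 3
- Actigraphy sleep: SO, TST, WASO, SE = 4 (given as examples, so the list is open)
- Non-parametric rhythm: IV, IS, RA = 3
- Activity time: sedentary, MVPA = 2

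Total 3 + 4 + 3 + 2 = 12. Table 1 schedules MEQ and SPAQ at baseline only, so they have no change score. The change-on-change model in the analysis section can therefore use 12 − 2 = 10. Twelve applies if baseline level is the predictor, which the wording of the objective allows.

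**3. Scale of the problem.** Suppose each measure is tested once at 5% against the one composite and all nulls are true. Under independence, the chance of at least one false positive is 1 − 0.95^k:
- k = 10: 1 − 0.5987 = 40%
- k = 12: 1 − 0.5404 = 46%

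The documents give no correlations between these measures, so a range is assumed. Simulation of k equally correlated two-sided z-tests (400,000 draws) gives:

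| Assumed pairwise correlation | 10 tests | 12 tests |
|---|---|---|
| 0.3 | 35.1% | 39.8% |
| 0.5 | 28.8% | 31.9% |
| 0.7 | 21.3% | 23.2% |

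**4. What the figures leave out.** They count one test per measure. They add nothing for the two follow-ups, for the adjustment models, or for a method changed after the results are seen. The last of these has no computable error rate, because the set of possible methods is not defined.

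**5. Internal consistency.** A primary hypothesis, a primary outcome, a powered sample size and a test of significant prediction are confirmatory language. The exploratory description in the Discussion is not. Both stand in the same article.

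**The case against.** The strongest reply is that only a journal article is at hand. A primary exposure, a primary model and a multiplicity rule are often left to the full protocol or analysis plan. That stands: their absence alone is not a finding. The point rests on the Discussion sentence, which is stated, and on its combination with unranked exposures and confirmatory language.

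A second reply is that the sentence may mean only adapting to the data's distribution, since histograms and a Shapiro-Wilk test are planned, and that the study calls itself exploratory. The benign reading is possible, but the sentence names the results and sets no such limit. The exploratory label would excuse the lack of error control if it were applied throughout; here it conflicts with the rest of the text.

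A reader might also infer more than the documents support:
- **A 71% error rate from 12 measures × 2 follow-ups = 24 independent tests.** MEQ and SPAQ have no follow-up values, a mixed model can take both follow-ups in one test, and measures drawn from one actigraphy record are unlikely to be independent.
- **That each adjustment model is another route to success.** The article describes these models as robustness checks.
- **That the mood correlations inflate the error rate of the hypothesis.** The plan for "correlating these difference scores (baseline minus 6-month follow-up, baseline minus 12-month follow-up) with circadian rhythm parameters for each participant" concerns anxiety, depression and mania scales. It does not test the cognitive hypothesis.
- **That any one significant test counts as success.** The article states no such rule; the figures above show only what would follow if it were applied.

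The count of 12 can also be disputed. If only IV, IS and RA represent circadian rhythm, the figure under independence is 1 − 0.95³ = 14%. That is smaller but still above 5%, and nothing in the article makes this narrower choice.

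**Conclusion.** The concern holds in this form: the article permits a results-driven choice of method, leaves 12 circadian measures unranked (10 with a change score), and still speaks of a primary hypothesis and significant prediction. A significant result could therefore not support that hypothesis at a known error rate.

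The illustrative size is 40% (10 tests) or 46% (12 tests) under independence, and about 23% to 40% for 12 tests at correlations of 0.3 to 0.7. These rest on one unadjusted 5% test per measure, all nulls true, and correlations that are assumed. They show scale; they are not the study's actual error rate, which the plan leaves undefined. It would go too far to say that every p-value in the study is meaningless: descriptive and openly exploratory results are not affected in the same way. That the sample size calculation contains no circadian term is a separate matter and is used here only to show where the alpha belongs.

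**What to change.** Delete the Discussion sentence and choose one of two routes.

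- **Keep a confirmatory claim.** Name one circadian exposure and its form (baseline level or change), tested against 12-month change in the cognitive composite in one named, adjusted mixed model. Fix this before any association between circadian measures and follow-up cognition is examined. A lock set only before the 12-month analysis would be too late, because the 6-month associations could then guide the choice. Label all other exposures, time points and models exploratory, and report any later change of method as post hoc with its reason.
- **Declare the whole study exploratory.** Remove the primary-hypothesis and significance language, present estimates with intervals, and still report departures from the plan as post hoc.

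Either route changes wording only; no design, visit or measurement is affected. The cost is that only one exposure, or under the second route none, can support a confirmatory claim.

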## Data Availability

Not applicable.
